#### Participant timeline {13}

As shown in Table 2.

**Table 2 Tab2:** Participant timeline {13}

Study period			
Timepoint	Pre-study screening/consent	Study	Follow-up
	−1~0	1~7	8~9
Eligibility screen	×		
Informed consent	×		
Allocation	×		
Demographic information	×		
Medical history and treatment history	×		
Inclusion/exclusion form	×		
Vital signs	×	×	×
Mechanical ventilation		×	
Haematology(RBC/WBC/PLT/HBG)	×		
Coagulation(PT/APTT/FIB/D-Dimer/INR)	×		
Observe the catheter scale	×	×	
Intervention		×	
Assessing catheter patency	×	×	
Complication records	×	×	×
Adverse event		×	×
Medication record		×	
Catheter removal record		×	
Consumables		×	
Operation time		×	
Research summary			×

#### Sample size {14}

The primary outcome is the rate of catheter occlusion within 7 days. A preliminary study with a small number of patients (20 patients) indicated that the catheter occlusion rate was 0 in the test group and 20% in the control group. According to an expert consensus [7], the occlusion rate in the control group ranged from 25 to 38%. Using an estimation procedure based on the differences between the two groups, the necessary sample size was determined. An occlusion rate of 10% was assumed in the test group, and an occlusion rate of 25% was assumed in the control group. A minimum sample size of 125 participants per group (250 participants total) was calculated by PASS 15 software (NCSS, LLC) to provide sufficient statistical power for detecting the difference between the two groups. This was done by setting the single-sided significance level (*α*) at 0.025 and the statistical power (1-*β*) at 0.8 while taking into consideration a dropout rate of 20%.

The sample size was calculated as follows:$${n}_{T} = {n}_{C}=\frac{{({Z}_{1-a/2}+ {Z}_{1-\beta })}^{2} \left[{P}_{C}\left(1-{P}_{C}\right)+{P}_{T}(1-{P}_{T}) \right]}{{\left(\left|D\right|-\Delta \right)}^{2}}$$

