### Assignment of interventions: allocation

#### Sequence generation {16a}

Before the start of the study, the statistics team will perform randomization using a computer-generated random assignment list at a 1:1 ratio.

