### Statistical methods

#### Statistical methods for primary and secondary outcomes {20a}

The primary outcome of this study is the occlusion rate in 7 days. The calculation formula is:$$\mathrm{Occlusion}\;\mathrm{rate}=\frac{\mathrm{Complete}\;\mathrm{occlusion}+\mathrm{Partial}\;\mathrm{occlusion}}{\mathrm{Number}\;\mathrm{of}\;\mathrm{enrolled}\;\mathrm{cases}}\times100\%$$

A superiority test will be conducted on the occlusion rate of the two groups. The chi-square test will be used to compare the occlusion rates between the two groups. The occlusion rate and 95% confidence interval will be calculated for the intervention group. Simultaneously, the 95% confidence intervals (CIs) for the difference in the occlusion rate between the test group and the control group will be calculated. If the upper limit of the confidence interval is less than the superiority threshold (0), the conclusion of superiority is deemed valid.

Validity analysis will be conducted on both the full analysis set (FAS) and per protocol set (PPS). All baseline demographic data analysis will be conducted on the FAS, and safety evaluations will be based on the safety analysis set. The FAS refers to the set of subjects analysed according to the intention-to-treat (ITT) principle, including all subjects who will be randomized and intervened. For subjects who failed to complete the full efficacy evaluation, non-responder imputation (NRI) will be used to handle the missing data.

With respect to the secondary outcomes, comparisons between the two groups will be made using the group *t* test or Wilcoxon rank-sum test for measurement data according to distribution and the chi-square test or Fisher’s exact probability method for count data. 

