#### Methods in analysis to handle protocol non-adherence and any statistical methods to handle missing data {20c}

For possible missing data during the study, the analysis will be carried forward for missing primary outcomes, and the specific carryover method is described in “Statistical methods for primary and secondary outcomes {20a}” section. Catheter occlusion is defined as a partial or complete occlusion of an intravascular catheter, resulting in blocked or restricted infusion of fluid or medication. For subjects who failed to complete the primary outcome evaluation, the method of worst-case imputation will be used to handle missing values. That is, if subjects withdraw early or for any other reason and the primary outcome is missing, the decision of whether or not catheter occlusion occurred will be treated as occlusion.

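### The stated 80% power fits an analysis that leaves dropouts out; the FAS analysis, which scores them as occlusions, has about 52% power at the planned 20% dropout

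*Protocol article*

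**What the plan says.** Protocol article, Sample size {14}: "An occlusion rate of 10% was assumed in the test group", and "an occlusion rate of 25% was assumed in the control group". The calculation is described as "setting the single-sided significance level (*α*) at 0.025" and "the statistical power (1-*β*) at 0.8 while taking into consideration a dropout rate of 20"%. The result: "A minimum sample size of 125 participants per group (250 participants total) was calculated by PASS 15 software".

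Statistical methods {20a}: "Validity analysis will be conducted on both the full analysis set (FAS) and per protocol set (PPS"). The FAS is all patients randomized and given the intervention. The primary occlusion rate is divided by enrolled cases, and incomplete efficacy evaluations are handled by non-responder imputation. Superiority is concluded if the upper 95% confidence limit for the difference (test minus control) lies below 0. A chi-square test is also specified.

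Missing data {20c}: if a patient leaves early, or the primary outcome is missing for any other reason, "the decision of whether or not catheter occlusion occurred will be treated as occlusion".

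Intervention description {11a}: a patient whose catheter is removed for other reasons, with no occlusion seen, counts as a dropout.

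**The concern.** Dividing a sample size by one minus the dropout rate is right when dropouts disappear from the analysis and the assumed rates hold in those who remain. Here that describes a completers-type comparison such as the PPS. In the FAS, dropouts stay in the denominator and each adds an event. Adding the same proportion of events to both groups pulls the two rates together and moves them towards 50%, where the variance is larger. Both changes cost power, and section {14} allows for neither.

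The problem does not need unequal dropout between the groups, and it does not depend on whether worst-case imputation is a good rule. The printed power simply belongs to a different analysis from the FAS one. A reader who trusts 80% would take a non-significant FAS result as fair evidence against the intervention, although that analysis had roughly even odds of detecting the planned effect.

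**Working it through.** **Inputs.** From {14}: control 25%, test 10%, one-sided alpha 0.025, power 0.8, dropout 20%, 125 per group. From {16a}: 1:1 allocation. From {20a}: superiority threshold 0. From {20c}: missing outcome counted as occlusion. Assumption: dropout is 20% in each group, since the article gives no split by group.

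**1. Reproduce the plan's figure.** Pooled two-proportion formula, with mean rate (0.25 + 0.10)/2 = 0.175:

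n = [1.960 × √(2 × 0.175 × 0.825) + 0.842 × √(0.25 × 0.75 + 0.10 × 0.90)]² / 0.15² = 99.5, so 100 per group.

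100 / (1 − 0.20) = 125, an exact match. The unpooled formula printed in {14}, with margin 0 and z at 0.975, gives 96.8, so 97 per group, and 97/0.8 rounds up to 122. Either way, dropouts are treated as removed. Power for 100 evaluable per group at 10% v 25% is 80.2% (pooled normal approximation) or 81.6% (exact chi-square).

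**2. Rates that the FAS compares.** With dropout d scored as occlusion, the rate is (1 − d) × p + d:

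- Test: 0.8 × 0.10 + 0.20 = 0.28
- Control: 0.8 × 0.25 + 0.20 = 0.40
- Difference: 12 points instead of 15

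**3. FAS power at 125 per group.** Pooled normal approximation, with mean rate 0.34:

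- Standard error under no difference: √(2 × 0.34 × 0.66 / 125) = 0.0599; times 1.960 = 0.1174
- Standard error under the alternative: √((0.40 × 0.60 + 0.28 × 0.72)/125) = 0.0594
- Power = Φ((0.12 − 0.1174)/0.0594) = Φ(0.043) = 51.7%

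Exact binomial enumeration gives 52.3% for the chi-square test and 52.8% for the rule that the upper Wald 95% limit is below 0. The false-positive rate of that rule is about 0.025, so a mismatch in alpha or sidedness does not explain the gap.

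**4. Other dropout rates, equal in both groups, 125 per group.**

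| Dropout | FAS rates, test v control | Exact power, chi-square | Exact power, Wald limit |
|---|---|---|---|
| 5% | 14.5% v 28.75% | 78.7% | 79.5% |
| 10% | 19% v 32.5% | 68.9% | 69.6% |
| 20% | 28% v 40% | 52.3% | 52.8% |

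The stated power is therefore roughly right for the FAS only at about 5% dropout or less. For scale, 80% FAS power at 20% dropout would need about 244 per group (pooled formula).

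**5. Other ways to model dropout.**

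- If 20% of the non-occluded patients drop out, the rates are 0.10 + 0.2 × 0.90 = 0.28 and 0.25 + 0.2 × 0.75 = 0.40, the same as above.
- If every assumed occlusion is still observed and a further 20% of each group drops out, the rates are 30% v 45% and power is 69%.
- If dropout is unequal, power moves strongly: 25% control and 15% test gives 93%; 15% control and 25% test gives 9%.

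**The case against.** The strongest reply is that 52% depends on a dropout model that the article does not fix. Because a patient's participation ends at occlusion, one could argue that all the assumed occlusions are observed and dropouts come on top, which gives 69%. This has some force: the figure should be quoted with its assumption. But 30% v 45% with 20% missing implies 0.10/0.80 = 12.5% v 0.25/0.80 = 31.25% among evaluable patients, which is not the 10% v 25% that {14} applies to the 100 left after dropout. Even 69% is well below 80%.

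Second, the FAS is not named as the primary set, and 80% is right for a PPS-type comparison. That is true, and nothing in {14} is miscalculated for such an analysis. But {20a} specifies the FAS for efficacy and divides by enrolled cases, and {14} does not say that its power excludes the FAS.

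Third, 20% is a planning allowance, and section {18b} selects patients expected to keep the catheter more than 8 days in order to limit dropout. Actual dropout may be lower, and the loss of power with it. That is a reason to show power over a range, not to leave 80% unqualified.

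Fourth, unequal dropout would matter more than anything above. This is correct, but it is a separate question; the plan assumes no difference between groups.

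**Conclusion.** The concern holds. The sample size reproduces exactly as 100 evaluable per group inflated to 125, so the 80% is the power of an analysis that excludes dropouts. For the FAS with missing outcomes scored as occlusion, power at the plan's own 20% dropout is about 52% (52.3% by chi-square, 52.8% by the confidence-limit rule). This rests on equal dropout in both groups and on 10% v 25% holding among evaluable patients. Under the most favourable equal-dropout model examined it is 69%. The conclusion that the FAS falls well short of the stated power at 20% dropout does not depend on the choice between these models. It also does not depend on which analysis set is primary.

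**What to change.** In Sample size {14}, state power by analysis set:

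- 125 per group gives about 80% power for the evaluable-patient (PPS) comparison after 20% dropout.
- 125 per group gives about 52% power for the FAS at 20% dropout with missing outcomes counted as occlusion. Give the values at 5% (about 79%) and 10% (about 69% to 70%) beside it.
- These figures assume equal dropout in the two groups and 10% v 25% among evaluable patients.
- A non-significant FAS result at 20% dropout is not evidence of no effect.

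The cost is a few sentences and a less favourable power figure for the FAS. No extra patients, no new procedures and no change to the imputation rule are needed. The Trial status section gives recruitment as completed in June 2023, so the benefit lies in how the result is read.

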#### Recruitment {15}

Patient recruitment will be conducted at 14 medical centres in 3 provinces, Jiangsu, Anhui, and Hunan provinces, in China, and recruitment will be carried out for critically ill patients using CVC. Recruitment began in February 2023, and the study is scheduled to be completed within 3 months. Each centre plans to enrol 18 patients, which means that each centre will enrol 6 patients per month.

### Assignment of interventions: allocation

#### Sequence generation {16a}

Before the start of the study, the statistics team will perform randomization using a computer-generated random assignment list at a 1:1 ratio.

#### Concealment mechanism {16b}

The statistics team will generate random numbers and will hand them over to people unrelated to the study, who will then make sealed, opaque envelopes, and send them to each centre in order of the centres’ initials. Each centre will receive 18 envelopes. The random envelopes will be kept by the principal investigators (PIs) of each centre and will not be accessible to persons unrelated to this study. The statistics team will not be involved in clinical trials.

#### Implementation {16c}

The SIs are responsible for enrolling the subjects. After the patient signs the informed consent form, the SIs will assess the patient's eligibility for enrolment. For patients eligible for enrolment, the random envelope will be opened in the order of enrolment to obtain a unique random number.

### Assignment of interventions: blinding

#### Who will be blinded {17a}

It is difficult to blind participants and study investigators in this study, but the data analysts will be blinded. Data analysts will not participate in the clinical trial process, and they will not know the interventions used in the two groups.

#### Procedure for unblinding if needed {17b}

The design is open label, so unblinding will not occur.

### Data collection and management

#### Plans for assessment and collection of outcomes {18a}

We held 13 online training sessions to conduct case report form (CRF) completing, trial procure, participant assessment, and other relevant details. Before the trial begins, every centre will receive on-site instruction, and they will be encouraged to complete a pretest to ensure familiarity with the process. All the data will be entered into an electronic database by two trained researchers.

#### Plans to promote participant retention and complete follow-up {18b}

The objective of the study is to compare the effects of two flushing techniques over 7 days. To minimize the dropout rate, patients with a CVC usage duration of more than 8 days must be selected during the screening process. Given that the study cannot intentionally prolong the patient’s catheter-wearing time, the challenging task of selecting eligible patients is entrusted to the head nurses, who are well versed in clinical work. For those patients who are transferred within the hospital and have an intervention time of less than 7 days, the study will continue to track them unless they are discharged or transferred to another hospital.

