**Method:**

This is a randomized controlled trial of 14 hospitals in China. A total of 250 patients will be recruited in this study, and they will be randomized at a 1:1 ratio. After study inclusion, patients who will undergo CVC insertion will receive intermittent flushing with prefilled saline syringes (control group) or KVO infusion with elastic pumps (test group). All the catheters will be checked for patency by scoping Catheter Injection and Aspiration (CINAS) Classification on Days 3 and 7. The primary outcome is the rate of catheter occlusion in 7 days. Patients will be followed up until 9 days after CVC insertion, catheter occlusion, or catheter removal. The secondary outcomes are the rate of catheter occlusion in 3 days, nurse satisfaction, cost-effectiveness, adverse event rate, catheter-related bloodstream infection rate, catheter-related thrombosis rate, extravasation rate, phlebitis rate, and catheter migration.

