In the control group, prefilled saline syringes containing 10 ml of 0.9% sodium chloride injection will be used to flush and lock the catheter via pulsatile flushing and the positive pressure locking technique. Before each infusion, the study nurses will mechanically wipe and sterilize the infusion connector. Catheter function will be assessed by flushing the catheters and aspirating for blood return. After seeing the blood return, the catheter will be flushed using short-interval pulsatile flushing (1 ml each time), for a total of 10 ml [22]. At the end of the infusion, prefilled saline syringes will be used to flush each lumen (even if only one lumen is used) via pulsatile flushing and the positive pressure technique [24].

The study will continue for 7 days unless there is catheter occlusion or catheter removal. During the 7 days, the study nurses will identify catheter occlusion by scoping the CINAS, observing the infusion status, and identifying the occlusion alarm. Once catheter occlusion occurs, the patients reach the end of the study, and the management of the blocked catheter will be referred to the physician and nurse. The end of the trial also includes a 2-day observation period, which will monitor the occurrence of catheter-related bloodstream infection (CRBSI), primarily through temperature monitoring.

Throughout the trial, the study team will fully respect the patient’s wishes, and the patients will have the right to withdraw from the trial. In addition, if a patient has no observed occlusion during the trial period and removes the CVC for other reasons, then the patient will be considered to have dropped out.

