#### Criteria for discontinuing or modifying allocated interventions {11b}

The intervention will stop in the following circumstances:

Patients who developed planned or unplanned catheter removal;Discharge, death, deterioration of the condition;Patients withdraw proactively;Wrong intervention.

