#### Adverse events reporting and harms {22}

The expected possible complications include catheter occlusion, catheter-related bloodstream infection, thrombosis, and catheter prolapse. All adverse events and unexpected consequences will be evaluated and recorded. The study nurses will monitor the occurrence of complications daily. If an adverse event occurs, the study nurses will report the situation, outcome, and relationship with the trial. In the event of a serious adverse event, the clinical research coordinator will assist the investigator in filling out the “Serious Adverse Event Report Form” as soon as possible, reporting it to the institution’s office and ethics committee, and faxing it to the national State Food and Drug Administration (SFDA), Jiangsu SFDA, and sponsor within 24 h and retaining the fax record.

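### No patency check is stated at planned removal, discharge or transfer out, so catheters that could have been shown patent are scored as occluded

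*Protocol article*

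**What the plan says.** **When patency is checked.** The abstract (Method) fixes two dates: "All the catheters will be checked for patency by scoping Catheter Injection and Aspiration (CINAS) Classification on Days 3 and 7". Section {11a} adds surveillance over the 7 days, without dates: "the study nurses will identify catheter occlusion by scoping the CINAS, observing the infusion status, and identifying the occlusion alarm". In the control arm, before each infusion, "Catheter function will be assessed by flushing the catheters and aspirating for blood return". Table 2 in {13} marks patency assessment and a catheter removal record across Days 1 to 7. Section {22} lists occlusion among the expected complications and says "The study nurses will monitor the occurrence of complications daily". No section states a CINAS at the moment of planned removal, discharge or transfer out.

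**When follow-up ends.** The abstract says "Patients will be followed up until 9 days after CVC insertion, catheter occlusion, or catheter removal", and {11a} runs the study for 7 days unless the catheter occludes or is removed. Section {11b} stops the intervention for planned or unplanned removal and for "Discharge, death, deterioration of the condition;Patients withdraw proactively;Wrong intervention". It does not say whether outcome assessment continues after such a stop. Section {18b} takes up one case, patients moved within the hospital with less than 7 days of intervention: "the study will continue to track them unless they are discharged or transferred to another hospital".

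**How an early exit is scored.** Section {11a} classes removal for other reasons, with no occlusion observed, as dropout. Section {20c} treats a missing primary outcome as occlusion. Section {20a} keeps these patients in the full analysis set and divides by the number enrolled.

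**The concern.** The primary outcome is occlusion by Day 7, and partial occlusion counts. A catheter that works when it is electively removed on Day 6 has its last dated CINAS on Day 3. With no exit check stated, its Day 7 outcome is missing and becomes an occlusion. A nurse could have recorded its working state minutes before removal.

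A second group stops the technique with the catheter still in place, for example after a wrong intervention or a deterioration. The general follow-up statements cover them, but the retention section names only in-hospital transfers, so a site could reasonably stop assessing them. Their outcomes would then be imputed too.

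At stake is how many primary-endpoint events are real. Imputed events added to both arms dilute the difference the trial was sized to find. If the arms lose patients at different rates, which is possible in an open-label comparison, imputed events also shift the difference itself.

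**Working it through.** **Inputs** (all from Sample size {14}): occlusion 10% in the test arm and 25% in control; one-sided alpha 0.025 (critical value 1.96); power 0.80; dropout 20%; 125 per arm.

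**Step 1. Reproduce the plan's figure.** With pooled variance under the null, p̄ = 0.175:

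n = [1.96·√(2·0.175·0.825) + 0.842·√(0.25·0.75 + 0.10·0.90)]² / 0.15² = (1.053 + 0.443)² / 0.0225 ≈ 99.5, so 100 per arm. Then 100 / 0.8 = 125, which matches. (The unpooled formula printed in {14}, with the same critical value, gives 97, then 122.) This inflation treats dropouts as leaving the analysis: 100 evaluable per arm give 80.2% power.

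**Step 2. Apply the stated scoring rule.** Dropouts stay in and count as occluded. If dropout d is equal in both arms and unrelated to occlusion, p* = p(1 − d) + d. At d = 0.20:

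- Test: 0.10·0.80 + 0.20 = 0.28
- Control: 0.25·0.80 + 0.20 = 0.40

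Per 125 patients, the test arm has 35 events, of which 0.20·125 = 25 are imputed. Control has 50, of which 25 are imputed. The difference falls from 15 to 12 points.

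**Step 3. Power at 125 per arm.**

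Power = Φ{[D√n − 1.96·√(2p̄(1 − p̄))] / √(pT(1 − pT) + pC(1 − pC))}

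With D = 0.12 and p̄ = 0.34: (0.12·11.180 − 1.96·0.670) / 0.6645 ≈ 0.043, and Φ(0.043) = 51.7%.

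**Step 4. Vary the share of dropouts whose outcome is measured.** The article does not give this share, so the full range is shown. Measured patients are assumed to have the planned rates.

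| Dropouts measured | Still imputed | Test | Control | Power |
|---|---|---|---|---|
| 0% | 20% | 28% | 40% | 51.7% |
| 25% | 15% | 23.5% | 36.25% | 59.7% |
| 50% | 10% | 19% | 32.5% | 68.7% |
| 75% | 5% | 14.5% | 28.75% | 78.5% |
| 100% | 0% | 10% | 25% | 88.2% |

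The lower rows are approximate. A patient measured at exit has had less than 7 days at risk, so the rates in that group would be somewhat lower than assumed.

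**Step 5. Unequal loss, as illustration only.** Suppose both true rates are 25%, with 25% of control and 15% of test patients imputed. The scored rates are 0.25·0.75 + 0.25 = 43.75% and 0.25·0.85 + 0.15 = 36.25%. That is a 7.5-point apparent benefit, significant in favour of the test arm about 23% of the time. The article gives no dropout split by arm, so this is an assumption.

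**The case against.** Much of the opposing case stands, and it rules out several stronger readings.

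- **Patency is measured only on Days 3 and 7, so early stoppers have no measured outcome.** A reader might infer this from the abstract. Sections {11a}, {13} and {22} contradict it: occlusion is looked for throughout the 7 days, and a patient who stops early may have an observed occlusion or a Day 3 CINAS. What may be lacking is status at exit and at Day 7.
- **The test arm has no aspiration check between those days.** The CINAS surveillance in {11a} is not limited to one arm, and CINAS grades aspiration ({12}). It remains true that its timing is not fixed, and that the only check tied to a routine event, before each infusion, is described for control.
- **Follow-up ends when the technique stops.** Section {11b} stops the intervention, and the general follow-up statements make no exception for such a stop. The in-hospital transfer provision does not say that others are dropped. The gap is one of clarity.
- **The catheter is always there to test.** It is not after death, accidental dislodgement or departure. Nor can further checks be assumed in someone who withdraws from the trial.
- **An unseen occlusion at removal is lost.** Under {20c} it is already counted as an occlusion. The error runs the other way: patent catheters are counted as occluded.

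Three further points have weight. The power loss comes from the missing exit check and the scoring rule acting together, and cannot be charged to the first alone. Patency at exit is not Day 7 status, so the all-occluded rule has some merit as a cautious choice. Section {18b} also selects patients expected to keep the catheter beyond 8 days, which should limit early removals, although 20% dropout is still planned.

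It can also be said that exit procedures belong in a fuller protocol, and the content of the removal record is not shown. But this article itself defines the dropout, the imputation and the tracking provision, and together these score a working catheter as a failure.

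**Conclusion.** The point holds in this limited form: no CINAS is stated at planned removal, discharge or transfer out; continued tracking is spelled out only for in-hospital transfers; and the dropout and missing-data rules then turn catheters that could have been shown patent into occlusions.

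At the planned 20% dropout, equal in both arms and all scored as occluded, the rates move from 10% and 25% to 28% and 40%, and power is about 52%. This is the upper bound on the loss at that dropout. The true loss depends on how many exits could have been measured, which the article does not state. It also rests on the planned rates being true and on dropout being unrelated to occlusion. It does not show that the result is biased: that would need unequal loss between arms, for which the article offers no evidence.

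**What to change.** For the design:

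1. State in {11b} and {18b} that stopping the allocated technique does not end outcome assessment while the catheter is in place and the patient still consents to observation.
2. Add one CINAS in both arms immediately before planned removal, discharge or transfer out, recorded with date, time and reason.
3. Use that measured status in the primary analysis. Restrict imputation under {20c} to patients with no CINAS at exit, and keep the all-occluded rule as a sensitivity analysis.

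The cost is protocol and CRF wording, plus a short bedside check by study nurses already present, for at most about 50 patients (0.20 × 250). There are two downsides to disclose: exit status covers less than 7 days of exposure, and outcomes measured after a stop partly reflect routine care.

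For this trial, Trial status lists data collection as complete on July 31, 2023, so checks cannot be added. The sponsor should use any patency record made at exit and report the number of imputed primary outcomes by arm and reason.
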